### Statistical analysis

Analyses will be performed using Stata software. All data will be analyzed by intention-to-treat. The tests are two-sided, with a type I-error set at α = 0.05. Baseline characteristics (schools and children) will be presented as mean ± standard deviation (SD) or median [interquartile range] for continuous data and as number of patients and associated percentages for categorical parameters. Hierarchical generalized linear regression models (mixed models with logit link function for dichotomous dependant endpoint), with levels (random-effects) for schools, classes and children, and repeated measurements, will be used to estimate effect of the intervention on smoking prevalence. These models (intercept and slope as random effects for longitudinal analyses) include an interaction between randomization group and time-points evaluation, and will be adjusted on initial consumption (occasional smoking or daily smoking) and other epidemiological relevant parameters (duration and typology of smoking habits): age of first consumption, gender of children and school’s characteristics. Intra-class correlation coefficients will be presented by arm and results are described as odds-ratios and 95% confidence intervals.

The secondary analyses will compare changes between groups with random effect models (1) to measure the behaviors with regards to tobacco and cannabis consumption and their evolution over a period of two years and (2) to determine predictive factors of tobacco consumption.

The behaviors regarding smoking having theoretically been well differentiated in this population according to gender, a subgroup analysis will be explored as described previously.

To assess the problem caused by missing data (schools, classes and/or children), estimation methods developed by G. Verbeke and G. Molenberghs [75] will be proposed after sensitivity analyses particularly appropriate to measure the nature of missing data (missing at random or not).

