### Objectives

The primary objective of this study is to measure the 24-month impact of a peer intervention based on the TPB on a highly exposed young population (from Languedoc-Roussillon vocational schools) by reaching a 10% difference in daily smoking prevalence between interventional and control groups after two-years.

Secondary objectives are to increase intention to not start smoking and/or intention to diminish tobacco consumption. This study aims to modify norms in favor of a tobacco non-consumption: behavioral norms (“I see benefits”), normative beliefs (“my parents and friend(s) would approve”), control beliefs (“I recognize the difficulties and I feel able to overcome them”), attitudes (“I am in favor to do so”), subjective norms (“I am approved by people that are important to me”) and perceived control (“I feel capable of doing this”).

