### Outcome measures

The **primary outcome measure** is the prevalence of daily smoking at 24 months defined by daily tobacco use of at least 1 cigarette validated by CO levels in exhaled air.

The **secondary outcome measures** are: using habits (tobacco, alcohol, cannabis); tobacco consumption modification characteristics (decrease, quitting); tobacco addiction and CAST score, elements of TPB (behavioral norms, normative beliefs, control beliefs, attitudes, subjective norms, and perceived control); gender; environmental quality of high schools toward tobacco.

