#### Sample size

The sample size estimation has been carried out on the basis of the literature [73, 74], with a daily smoking prevalence at 43% and a minimal absolute difference at two years between intervention and control groups equaling 10% (cf. Fig. 2). The two-sided type I error and the statistical power are fixed respectively at 5% and 80%.

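### The objective is a 10-point prevalence difference at one time, but only conditional odds ratios are reported and no arm contrast at that time is named

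*Protocol article*

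**What the plan says.** Three sections of the protocol article put the target on the absolute prevalence scale at a single time.

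- Objectives: the 24-month impact is to be shown "by reaching a 10% difference in daily smoking prevalence between interventional and control groups after two-years".
- Outcome measures: the primary outcome "is the prevalence of daily smoking at 24 months defined by daily tobacco use of at least 1 cigarette validated by CO levels in exhaled" […].
- Sample size: the calculation works "with a daily smoking prevalence at 43"%, and the effect to be detected is "a minimal absolute difference at two years between intervention and control groups equaling 10"%.

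The Statistical analysis section works on another scale. It fixes a mixed model with a logit link, random effects for schools, classes and children, and repeated measurements. On treatment terms it says: "These models (intercept and slope as random effects for longitudinal analyses) include an interaction between randomization group and time-points evaluation". The same models "will be adjusted on initial consumption (occasional smoking or daily smoking"), among other covariates, and "results are described as odds-ratios and 95% confidence intervals". It mentions no risk difference, standardised prevalence or arm contrast at a given visit.

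The Follow up section lists four evaluations using the same measures, the first before the intervention starts. The later ones are at 3, 9 and 15 months.

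**The concern.** The trial's own success criterion is a population quantity: how many fewer students per hundred smoke daily. An odds ratio from a model with a child-level random effect compares the odds for a given child (same random effect, same covariates) under the two arms. The two differ whenever children vary, and the gap grows with that variation. Smoking status is persistent, so the child variance could be large. The reported odds ratio could then look much stronger than the population effect, and it could not be set against the 10 points on which the trial was sized.

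The treatment term adds a second ambiguity. A group-by-time interaction means different things depending on whether the baseline wave is in the response and whether time is categorical or linear. Under one of the open readings, a constant benefit at every follow-up would produce no interaction at all.

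**Working it through.** **1. The plan's own figures.** Inputs from Sample size: 43% against 33%, two-sided 5%, 80% power, class size 20 (SD 4.9), ICC 0.1, loss 25%. Equal allocation is assumed because no ratio is stated.

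- Pooled two-proportion formula: n per arm = [1.96√(2 × 0.38 × 0.62) + 0.842√(0.43 × 0.57 + 0.33 × 0.67)]² / 0.10² ≈ 369, or 738 in total (plan: 740).
- Inflation: cv = 4.9/20 = 0.245; 1 + (20(1 + 0.245²) − 1) × 0.1 = 3.020; 740 × 3.020 = 2235 (plan: 2240).
- Loss: 2240/0.75 = 2987 (plan: 3000).

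The figures reproduce, so the trial was sized on a marginal risk difference of 43% against 33%.

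**2. From prevalence difference to odds ratio.** Marginal odds ratio = (0.33/0.67)/(0.43/0.57) = 0.653.

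For a random intercept with variance σ², the prevalence at linear predictor η is P(η) = ∫ expit(η + σx) φ(x) dx. Solve P(η_C) = 0.43 and P(η_T) = 0.33; the conditional odds ratio is exp(η_T − η_C). The article gives no variance, so σ² is an assumed range. The last column reverses the question: hold the control arm at 43% and apply a conditional odds ratio of 0.653.

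| Assumed σ² | σ²/(σ² + π²/3) | Conditional OR for 43% vs 33% | Points of prevalence if conditional OR = 0.653 |
|---|---|---|---|
| 0 | 0.00 | 0.653 | 10.0 |
| 0.37 | 0.10 | 0.631 | 9.3 |
| 1 | 0.23 | 0.599 | 8.4 |
| 4 | 0.55 | 0.499 | 6.2 |
| 8 | 0.71 | 0.416 | 5.0 |
| 20 | 0.86 | 0.281 | 3.4 |

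**3. What the interaction captures.** Suppose only follow-up waves are modelled, time is categorical, and the arm effect on the logit scale is β at every wave. With the first follow-up as reference, main effect = β and interaction = β − β = 0. The arm contrast at the last wave, main effect plus interaction, is still β. The interaction alone misses the effect; the contrast does not.

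If baseline is in the response and time is linear, take an effect of 0, 1, 1, 1 at months 0, 3, 9, 15. Least squares gives slope 6.75/132.75 = 0.0508 per month, so 15 × 0.0508 = 0.76 of the effect falls in the interaction and 0.75 − 0.0508 × 6.75 = 0.41 in the baseline group term, where the true difference is zero. This is a linear-scale illustration of why time should be categorical.

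**4. Baseline as covariate, outcome or both.** Fifteen simulated data sets per setting (3000 children, four visits, categorical time, child random intercept only) were fitted three ways. With assumed true variance 4 and a true last-visit odds ratio of 0.499:

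| Use of baseline | Last-visit group OR | Group × last-visit interaction (OR) | Estimated child variance |
|---|---|---|---|
| Covariate only | 0.502 | not applicable | 2.44 |
| Covariate and outcome | 0.496 | 0.489 | 1.02 |
| Outcome only | 0.510 | 0.491 | 4.03 |

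With true variance 8 the group odds ratios are 0.457, 0.452 and 0.453. All lie above the true 0.416, so only the comparison between fits is used here. The estimated variance falls from 3.68 (covariate only) to 1.74 (both). Double use hardly moves the group contrast but roughly halves the child variance. At variance 4, adjusting for baseline also leaves the odds ratio near 0.50, not 0.65, so adjustment does not bring it back to the marginal scale.

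**The case against.** Odds ratios are the ordinary output of a logit model, and the scale mismatch does not invalidate the test of no effect. Marginal prevalences and their difference can be derived from the fitted model, and a fuller analysis plan, not shown, may do so. The conditional odds ratios above rest on assumed variances. All of that stands.

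Three stronger readings are tempting, and the article does not support them.

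- A reader might infer that baseline smoking sits on both sides of the equation. Four evaluations with the same measures, a random slope and adjustment for initial consumption make this plausible, but the text never says the baseline record is in the response. If only follow-up waves are modelled, the adjustment is routine. Even under double use, the simulated group contrast barely moved (0.496 against 0.502), though that simulation had no school or class effects and no random slope.
- A reader might infer that the interaction is the primary test. The text says only that the models include it. With categorical time, the last-visit arm effect can be estimated from the same model.
- A reader might conclude that the model cannot deliver the primary quantity. It can, after one further step; the article does not name that step.

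The appeal to an unseen plan does not dispose of the rest. The article itself chose the model and the effect measure, and that measure does not answer the article's own objective.

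**Conclusion.** The concern holds as a mismatch between the stated objective and the stated report. It is not a claim that the model is invalid. Objective, outcome and sample size are an absolute 10-point difference at one time; the analysis commits only to odds ratios conditional on school, class and child, and names no arm contrast at that time. A conditional odds ratio of 0.653 could mean anything from 9.3 to 3.4 points over assumed variances of 0.37 to 20, so the odds ratio alone cannot show whether the objective was met. The size depends on a variance that the article does not give; the direction does not.

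The role of baseline and the status of the interaction are open questions in the text, not demonstrated errors. If baseline were used twice, the main casualty would be the child variance and any correlation coefficient derived from it, which matters because the article promises these coefficients by arm.

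A separate conflict limits any remedy: the outcome is defined at 24 months, while the last scheduled evaluation is at 15 months. No model of these data gives the 24-month prevalence without extrapolation.

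**What to change.** - Reconcile the 24-month outcome with the follow-up schedule ending at 15 months, so that the primary time point is fixed.
- Name the arm contrast at that time point as the primary test: main effect plus interaction, with time categorical.
- State that baseline smoking is a covariate only and that the response consists of the follow-up waves.
- Keep all follow-up waves in the model. With 25% loss expected, a model of the final wave alone would discard information from students who miss that visit.
- Report as the primary estimate the standardised prevalence difference. Average the predicted probabilities under each arm over the covariates and random effects, and give a 95% confidence interval that respects the randomisation of schools (about 14 are planned). Give the odds ratio alongside and say that it is conditional.

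The cost is a few sentences and one post-estimation step. No new data are needed.

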### Process evaluation

As emphasized by Hawe, Shiell, Riley and Gold [76], an evaluation of the implementation of an intervention in health education context is essential. Indeed, the pre-existing context can influence the effectiveness of the intervention. The method suggested by these authors is based on a mixed methodological approach, both qualitative and quantitative. We will assess a P2P program with vastly used items such as the course of actions and the mobilization of participants (see items 1 and 2 of Table 1 below). As promoted by Hawe et al. [76], we will also analyze how the intervention was implemented in context (see item 3). To this end, we will run a network analysis between major actors of the program: members of the school board, members of the educational staff (teachers, directors), teaching peers, beneficiary peers, and members of the technical committee. This will be achieved both in the control group (networks within the home school and inside the school) and in the intervention group (network among peers and with the project members) at the beginning, central and final steps of the program.

**Table 1 Tab1:** P2P process evaluation items

ITEMS	CRITERIA	INDICATORS	TOOLS
1. Did actions go according to plan?	• Compliance with provided protocol • Respect of schedule • Running in intervention and control groups	• Several steps • Step duration • Completion of each step • Measurement of deviation from the protocol	• Protocol drafting • Organization of indicators continuous reporting • Log book • Schedule
2. Did actions mobilize participants?	• Participation: - Project’s Technical Committee - Beneficiary peers - Teaching peers	• Regular attendance • Representativeness	• Attendance sheet
3. How did the actions take place in this context?	• Network analysis: - Members from the high school house of students - High-school teachers - Teaching peers - Beneficiary peers - Project’s technical committee	• Network density: number of contacts between members • Centralization: marginal or not based on the member’s role	• Individual meetings with key program actors • 3 evaluations (start, middle, and conclusion of the program)
4. How were the actions planned with the teaching peers?	• Issues and assets when taking actions • Teaching-peers needs • Relationship with technical committee	• Teaching peers needs analysis (relevance) • Adequacy of means to needs (consistency) • Review of actions	• Interviews with the teaching peers at the end of first year and second year of the program
5. How can the P2P program induce changes in high schools?	• Changes in the no smoking policy in high schools	• Changes in the high school students environment	• Number of changes • Time-scale change (short term, long term)

How actions took place with teaching peers is a crucial element for program success (see item 4). Thus, semi-structured interviews with teaching peers will be made to assess the issues and assets as well as the balance between the needs and the means at their disposal.

Finally, we will evaluate the events that might have occurred throughout the program such as the implementation of smoking cessation consultations in schools, the enforcement of no smoking rules in the facility, etc. (see item 5).

Qualitative data from the process evaluation will be subjected to a thematic content analysis. Key themes will be developed into an analytical grid. Each interview will be transcribed and coded into the grid themes. Quantitative data on fidelity and participation will be analyzed as covariate of outcome effects.

## Discussion

Smoking is a major challenge for public health and is associated with a range of factors. One of the most important factors is the environment, whether it is family, friends or peers. If the peer influence is normative and can encourage tobacco use, their influence against tobacco has been identified too. Prevention interventions, which promote these protective factors could have the potential to have a significant impact on the health and wellbeing of young people.

The P2P Program stemming from youth dynamism, its altruism and its new ways of communication [77] should boost the circulation of a validated piece of information into a risky population and its relatives, encouraging them to take into better account the major issues raised by smoking [39]. The very modernity of this program, with the original creation of a peer-based intervention mode that leads to a quality isometric confidence relationship between experts and public, should lead to the implementation of much appreciated interventions that fulfill the needs of the targeted population.

Prevention interventions need to be theoretically based during their development and to be evaluated with a rigorous methodology before expanding its implementation. This trial will assess the effectiveness of a prevention intervention based on the TPB. This theory has shown its effectiveness in predicting behavioral change and the not-starting-smoking-intent should reduce medium-term prevalence of smoking among the most exposed young people.

The results of this trial will help to inform future decision makers about the implementation of P2P in France.

If the P2P program shows an impact in the Languedoc-Roussillon region, larger-scale experimentation could reduce medium-term smoking prevalence among young people most at risk in all French regions. After this research, more actions could be performed or suggested: offering an effective methodology for prevention and assistance in quitting smoking to French national education and presenting it to prevention and health promotion actors.

In conclusion, this trial aims to evaluate P2P, a promising peer-to-peer program for prevention against tobacco for young people in vocational high schools and is based on the TPB. It is specifically designed to examine the relationship between trial outcomes and fidelity of implementation in a goal of efficacy and replicability.

## Abbreviations

MDL: Maison des lycéens (student house)
TPB: Theory of Planned Behavior
